**Figure 3. F3:**
[figure not shown]
The 5 auricular acupuncture points in this study. 1 = shenmen (TF4), 2 = lung (CO14), 3 = throat (TF3), 4 = inner nose (TG4), 5 = endocrine (CO18).

### 2.11. Outcome measurement

#### 2.11.1. Tobacco consumption and abstinence rate.

The primary outcome will be reductions in daily cigarette smoking, measured in the self-reported number of cigarettes smoked per day. The survey will be completed during visit 1, 4, 8, 9, and 10. The abstinence rate will be determined by the rate of change in the number of cigarettes smoked between the first and last visits (visit 10). Smoking cessation will be biochemically validated by a urine test. The subjects will be asked to submit the urine sample at visit 8 to 10.

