## Abstract

**Methods::**

This is a randomized, assessor-blind, and pragmatic pilot study. We will recruit 40 participants who want to stop smoking and randomly allocate them into an NRT group and an NRT + AA group with a 1:1 ratio. Participants will receive NRT for 4 weeks and the NRT + AA group will receive additional AA treatment with 5 AA points (Shenmen (TF4), lung (CO14), throat (TF3), inner nose (TG4), and endocrine (CO18)) twice a week for 4 weeks. Follow-up will be conducted 1 and 3 months after intervention completion. The primary outcome will be tobacco consumption and abstinence rate determined by calculating the rate of change in cigarette use and a urine test. Secondary outcomes will be the quality of life (EuroQol-5D and visual analogue scale), nicotine dependence (Fagerstrom test for nicotine dependence), nicotine withdrawal (Minnesota nicotine withdrawal scale), physical effects, satisfaction, and safety measurement (adverse events).

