### 2.12. Statistical analysis

We will express continuous variables as means ± standard deviation. For the statistical analysis, we will use paired *t* test for intra-group comparison and a 2-sample *t* test or Wilcoxon rank sum test for comparison between 2 groups. Categorical variables will be expressed as frequencies or percentages and tested statistically with the chi-squared test or Fisher’s exact test. All statistical analyses will be performed with the STATA version 15.0 (STATA Corp, LP. College Station, TX). Significance will be considered at a *P*-value < .05.

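### The abstinence rate is defined as a relative change in cigarette count, so it measures reduction in smoking and not the proportion who stopped

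*Protocol article*

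**What the plan says.** Section 2.11.1 opens with the primary outcome: "The primary outcome will be reductions in daily cigarette smoking, measured in the self-reported number of cigarettes smoked per day". Counts are collected at visits 1, 4, 8, 9 and 10. The section then gives a rule for a second quantity: "The abstinence rate will be determined by the rate of change in the number of cigarettes smoked", with visits 1 and 10 as the two time points. Two sentences on biochemical checking follow: "Smoking cessation will be biochemically validated by a urine test" and "The subjects will be asked to submit the urine sample at visit 8 to 10".

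The Abstract puts both quantities into the primary outcome and words them differently: "The primary outcome will be tobacco consumption and abstinence rate determined by calculating the rate of change in cigarette use and a urine test".

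Section 2.12 covers both types of variable. Continuous variables get a t test or Wilcoxon rank sum test between groups. For the others, "Categorical variables will be expressed as frequencies or percentages", with a chi-squared or Fisher's exact test.

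**The concern.** An abstinence rate is a count of people: those not smoking, divided by those in the arm. The rule in Section 2.11.1 is built from cigarettes. It takes the fall in daily count from visit 1 to visit 10, which is what the preceding primary outcome already measures, and expresses it relative to baseline. The section title and the Abstract promise two outcomes, consumption and abstinence, but the stated rules yield the same quantity twice.

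This is a stated rule, so it is not a detail left to a fuller document. The trial concerns smoking cessation, and the Abstract places abstinence in the primary outcome. If the rule is followed, partial reduction can appear under the label of abstinence, and a reader could take the result as a quit rate. The ranking of the two arms can also differ from their ranking on quitting.

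**Working it through.** The article states no figure that depends on this definition, so there is none to reproduce. The check applies the rule to assumed data and compares it with the proportion who stopped.

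**Inputs from the document.** 20 participants per arm (Section 2.5); entry at more than 10 cigarettes a day (Section 2.4.1); time points visit 1 and visit 10 (Section 2.11.1).

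**Assumptions.** Baseline of 20 a day unless stated otherwise, and all visit 10 counts. The article does not say whether the change is averaged over participants or taken on arm totals. With equal baselines the two give the same result.

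**Formulas.** Rule as written: R = mean of (C1 − C10)/C1, where C1 and C10 are the daily counts at visits 1 and 10. Proportion abstinent: p = (number with C10 = 0)/(number in arm). If r is the mean relative reduction among those who did not quit, then R = p + (1 − p) × r. So R equals p only if everyone quits or the non-quitters do not change on average.

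**Same rate, different quitting.**
- All 20 go from 20 to 10: R = (20 − 10)/20 = 50%; p = 0/20 = 0%.
- 10 quit, 10 unchanged: R = (10 × 100% + 10 × 0%)/20 = 50%; p = 10/20 = 50%.

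**Reversed ranking.**
- Arm A, all go from 20 to 4: R = 16/20 = 80%; p = 0/20 = 0%.
- Arm B, 8 quit and 12 unchanged: R = (8 × 100% + 12 × 0%)/20 = 40%; p = 8/20 = 40%.
- The rule puts A ahead of B, 80% to 40%. On quitting, B is ahead, 40% to 0% (Fisher's exact p = 0.003).

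**Range over baselines, with nobody quitting.**

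| Visit 10 count | Baseline 11 | Baseline 20 | Baseline 30 |
|---|---|---|---|
| 4 a day | 64% | 80% | 87% |
| 1 a day | 91% | 95% | 97% |

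Each cell is 1 − (visit 10 count)/(baseline). A baseline of 11 is the lowest whole number that meets the entry criterion. The true proportion abstinent is 0% in every cell.

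**Direction.** From R = p + (1 − p) × r, the rule overstates abstinence when non-quitters cut down on average (r > 0), agrees with it when they do not change, and understates it when they smoke more (r < 0).

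**The case against.** The strongest reply is that the urine test supplies the missing definition. The Abstract names it next to the rate of change, and can be read as assigning the rate of change to consumption and the urine test to abstinence. Section 2.11.1 speaks of biochemically validated cessation, and Section 2.12 has suitable tests for a categorical outcome. On this view validated quitters could be counted and compared under the existing text, and only one sentence is loosely worded.

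Part of this stands. A reader might infer that urine plays no role in abstinence, or that the trial could produce no cessation rate at all. The documents do not support either: the test is planned, and Section 2.12 contains no error and can handle a quit rate. But the favourable reading of the Abstract conflicts with the explicit rule in Section 2.11.1. That section leaves cessation undefined and does not connect a urine result to the abstinence rate.

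A second reply is that the outcome called primary in Section 2.11.1, reduction in self-reported cigarettes per day, is untouched. That is correct, and it limits the reach of the point. It does not remove it, because the Abstract makes abstinence part of the primary outcome.

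A reader might also infer that participants lost before visit 10 drop out of the calculation and inflate the rate, with the step from 12 to 20 per group implying a loss of 1 − 12/20 = 40%. The article gives no drop-out rate and no missing-data rule. Such a rule may stand in a document not shown, and the step to 20 is not a stated forecast. No attrition argument is made here.

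**Conclusion.** The point holds as a definition error. Section 2.11.1 calls a relative reduction in cigarette count an abstinence rate, no section defines abstinence as a proportion of participants, and the Abstract and Section 2.11.1 describe the outcome in ways that need reconciling.

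The size depends on how much non-quitters cut down. In the illustrations the gap runs from 0 percentage points (non-quitters unchanged) to 97 (everyone falls from 30 to 1 a day and nobody quits). These figures rest on assumed counts; that the rule measures reduction does not. It would go too far to say that the rule always gives a higher figure than the true proportion: the two agree when non-quitters do not change on average, and the order turns round if they smoke more. The sample size in Section 2.5 does not depend on this definition.

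**What to change.** Replace the rule in Section 2.11.1 with a binary outcome per participant at visit 10: zero self-reported cigarettes over a stated window, confirmed by the urine test already planned at that visit, against a stated criterion. The investigators need to supply the window and the criterion.

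Report the number abstinent divided by the number randomised in each arm. Compare arms with the chi-squared or Fisher's exact test already named in Section 2.12. Report the change in cigarettes per day only as reduction in consumption.

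Align the Abstract with Section 2.11.1, including whether abstinence belongs to the primary outcome and which measure the urine test serves.

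The cost is wording and a small amount of analysis. The cigarette counts and urine samples are already scheduled and the tests already named, so no visit or participant is added. Reported abstinence figures may differ from those under the current rule, and will often be lower, namely when non-quitters cut down on average.

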#### 2.11.2. Quality of life.

Quality of life will be measured by the EuroQol (EQ)-5D and the EQ-visual analogue scales (VAS) at visit 1, 4, 8, 9, and 10. EQ-5D is a generic measure of health status that can be used to clinically and economically evaluate health care and population health surveys.^[30]^ EQ-5D assesses health status in 5 dimensions: mobility, self-care, usual activities, pain and discomfort, anxiety, and depression. In EQ-VAS, participants will mark their overall daily health from 0 (worst) to 100 (best). In this study, higher scores will indicate a better quality of life.

#### 2.11.3. Nicotine dependence.

Nicotine dependence will be assessed using the Fagerstrom test for nicotine dependence at visit 1, 4, 8, 9, and 10. Fagerstrom test for nicotine dependence consists of 6 items that assess the period of heaviest smoking, including smoking when ill or smoking in places where it is prohibited.^[31]^ The 6 questions will be graded on a 2 to 4-point scale (0–1 to 0–3), which is summed to gain a total score (0–10). Higher scores indicate higher dependence.

#### 2.11.4. Nicotine withdrawal.

Nicotine withdrawal will be determined using the Minnesota nicotine withdrawal scale (MNWS), one of the most frequently used measures of nicotine withdrawal which generally reflect nicotine withdrawal syndrome symptoms in the DSM-IV.^[32]^ Each 9 withdrawal symptom (craving, irritability, anxiety, difficulty concentrating, restlessness, increased appetite or weight gain, depression, insomnia, and impatience) will be graded on a 5-point scale (1–5). Higher scores indicate a stronger nicotine withdrawal. The MNWS will be assessed at visit 1, 4, 8, 9, and 10.

#### 2.11.5. Physical effects.

The physical effects of smoking include irritability, tiredness, calmness, anxiety, cravings, unpleasant taste while smoking, headache, the ability to concentrate, and appetite. We will measure 4 domains that do not overlap with MNWS: tiredness, calmness, unpleasant taste while smoking, and headache, using a VAS from 0 to 100. Physical effects will be assessed at visit 1, 4, 8, 9, and 10.

#### 2.11.6. Satisfaction.

Satisfaction with NRT or NRT combined with AA treatment will be measured at the last treatment (visit 8) and during the follow-up phase (visit 9, 10).

#### 2.11.7. Safety measurement.

Adverse events will be assessed throughout the treatment period. Participants will be told to report information regarding adverse events and practitioners will follow up at regular or additional visits by several methods like clinical testing or history taking. All information, including the day of onset and disappearance, severance, relationship to the study, possible cause, and treatment, will be recorded.

### 2.12. Statistical analysis

We will express continuous variables as means ± standard deviation. For the statistical analysis, we will use paired *t* test for intra-group comparison and a 2-sample *t* test or Wilcoxon rank sum test for comparison between 2 groups. Categorical variables will be expressed as frequencies or percentages and tested statistically with the chi-squared test or Fisher’s exact test. All statistical analyses will be performed with the STATA version 15.0 (STATA Corp, LP. College Station, TX). Significance will be considered at a *P*-value < .05.

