#### 2.4.1. Inclusion criteria.

We will include subjects who:

•are 19 to 70 years old;•have no objection to nicotine patch and AA treatment;•have been smoking more than 10 cigarettes a day;•have attempted or are willing to quit smoking;•use nicotine patches to quit smoking or are willing to receive assistance; and•who voluntarily decided to participate in the clinical trial and provided written consent.

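### Section 2.12 fixes unadjusted between-arm tests and within-arm paired tests, although visit-1 values are collected: the first lose precision, and the second do not compare the arms

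*Protocol article*

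**What the plan says.** Section 2.12 names its methods for continuous outcomes. Within each arm it uses a paired t "test for intra-group comparison". Between arms it uses a two-sample t "test or Wilcoxon rank sum test for comparison between 2 groups". One threshold covers both: "Significance will be considered at a *P*-value < .05". No covariate, ANCOVA or repeated-measures model appears, and nothing says that the between-arm result carries the conclusion.

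Section 2.11.1 sets the schedule for the daily cigarette count: "The survey will be completed during visit 1, 4, 8, 9, and 10". Sections 2.11.2 to 2.11.5 use the same five visits for EQ-5D, EQ-VAS, the Fagerstrom test, the Minnesota scale and the four physical-effect scales. Satisfaction is the exception, with no visit-1 value.

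The primary outcome does make use of baseline. Section 2.11.1 states: "The primary outcome will be reductions in daily cigarette smoking, measured in the self-reported number of cigarettes smoked per day". It adds: "The abstinence rate will be determined by the rate of change in the number of cigarettes smoked between the first and last visits". No comparable change from visit 1 is defined for the secondary outcomes.

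Section 2.1 gives a comparative aim, the combination against NRT alone. Section 2.5 starts from 12, which I read as per arm, and recruits 20 per arm to allow for drop-out.

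**The concern.** There are two separate issues.

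**Precision between arms.** With 12 to 20 people per arm, chance differences at entry can be sizeable. Eligibility sets only a lower limit on consumption ("have been smoking more than 10 cigarettes a day"), so baseline counts may spread widely. A two-sample test on follow-up values leaves that spread in the error term. A test on change removes it by subtracting the whole baseline value, which over-corrects when the correlation is below 1 and the variances are equal. Adjusting for the visit-1 value uses the same data better. At stake is the width of the interval for the arm difference, which is the main quantitative product of a pilot.

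**Tests within arms.** Both arms receive patches, and both consist of people who smoke above a threshold and have tried or are willing to quit. Both can be expected to fall even if auricular acupuncture adds nothing. A paired test asks whether an arm changed, not whether the arms differ. If one arm crosses 0.05 and the other does not, the pattern is easily read as an effect of acupuncture. The Discussion expects the study to clarify efficacy for clinicians and policymakers, so that misreading would matter.

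**Working it through.** The article gives no effect size, SD, power or correlation for the analysis, so there is no planned figure to reproduce. The inputs are:

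- From the document: 20 per arm recruited and 12 as the starting number (section 2.5); threshold 0.05 (section 2.12).
- Assumed: a two-sided test; correlation r between baseline and follow-up of 0.3, 0.5 or 0.7; equal variances at the two times; the visit-1 value taken before the first treatment, since visit 1 is also a treatment visit.

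**1. Between-arm precision.** Relative to a follow-up-only comparison, the variance of the arm difference is 1 for follow-up only, 2(1 − r) for a change score and 1 − r² for ANCOVA. The ratio of ANCOVA to change score is (1 − r²) / [2(1 − r)] = (1 + r)/2.

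| r | Follow-up only | Change score | ANCOVA | ANCOVA / change | ANCOVA / follow-up |
|---|---|---|---|---|---|
| 0.3 | 1 | 1.40 | 0.91 | 0.65 | 0.91 |
| 0.5 | 1 | 1.00 | 0.75 | 0.75 | 0.75 |
| 0.7 | 1 | 0.60 | 0.51 | 0.85 | 0.51 |

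The reductions are therefore 35%, 25% and 15% against a change score, and 9%, 25% and 49% against follow-up only. At r = 0.5, 20 per arm with adjustment is worth 20/0.75 = 26.7 per arm without it.

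In terms of power, for an assumed difference of 0.8 SD of the follow-up value (normal approximation), going from change score to ANCOVA gives:

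- 20 per arm: 57% to 76% (r = 0.3), 72% to 83% (r = 0.5), 90% to 94% (r = 0.7). A follow-up-only test has 72% throughout.
- 12 per arm: 38% to 54%, 50% to 62%, 72% to 78%. A follow-up-only test has 50%.

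**2. Does the direction depend on equal variances?** Let σ₀ and σ₁ be the baseline and follow-up SDs. The change score has variance σ₀² + σ₁² − 2rσ₀σ₁, and ANCOVA has σ₁²(1 − r²). Their difference is σ₀² − 2rσ₀σ₁ + r²σ₁² = (σ₀ − rσ₁)², which is never negative. Against follow-up only the difference is r²σ₁², also never negative. Unequal variances alter the size of the gain against a change score but not its sign, apart from the one degree of freedom spent.

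**3. Within-arm tests when the arms do not differ.** Let both arms have the same true fall of k SDs of the change. Each paired test is significant with probability p, from a noncentral t with n − 1 degrees of freedom and noncentrality k√n. Exactly one arm is significant with probability 2p(1 − p).

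| k | n per arm | p | Exactly one arm significant |
|---|---|---|---|
| 0.5 | 20 | 0.565 | 2 × 0.565 × 0.435 = 49% |
| 0.5 | 12 | 0.353 | 2 × 0.353 × 0.647 = 46% |
| 0.8 | 20 | 0.924 | 14% |
| 0.8 | 12 | 0.714 | 41% |
| 1.0 | 20 | 0.989 | 2% |
| 1.0 | 12 | 0.883 | 21% |

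When the common fall is moderate, a split verdict between two arms with identical true change is close to a coin toss. When it is large, both arms are usually significant, which is equally uninformative about acupuncture.

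**The case against.** The best defence is that this is a pilot sized by a rule of thumb, with no power claim to undermine, and that the between-arm tests are sound under randomisation. Both statements are true, and they limit the weight of the point. They do not remove it: the stated aim is comparative efficacy, and the tests are fixed here rather than left to a later document.

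Several stronger readings are tempting, but the document does not support them:

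- A reader might infer that baseline is ignored. For the primary outcome it is not, because section 2.11.1 defines a reduction and a rate of change from the first visit. Nor does baseline imbalance pass straight into that result: with equal variances a change score carries it in the opposite direction with weight 1 − r.
- A reader might infer that none of the P-values compare the arms. Only the paired ones fail to. The rank-sum, two-sample t, chi-squared and Fisher tests are legitimate randomised comparisons; the unadjusted comparison is inefficient, not biased.
- A reader might take 49% as the loss for the primary outcome. It applies only against a follow-up-only test, at r = 0.7. Against an absolute reduction the figure at that correlation is 15%. The formulas do not cover a percentage change.
- A reader might count 9 outcomes × 4 visits × 2 arms = 72 paired tests. That is a ceiling; section 2.12 does not say that every combination will be tested.
- A reader might infer that participants who miss a visit are dropped. The article does not state how missing data are handled, and an article may leave that to the full protocol or analysis plan.

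A fair criticism of adjustment also stands in part. Cigarette counts may contain many zeros at follow-up, so normal-theory models are approximate and a rank test has a place. A repeated-measures model is not obligatory either: an unstructured covariance over four visits has 4 × 5/2 = 10 parameters to estimate from at most 40 people.

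**Conclusion.** The point holds as a matter of efficiency and interpretation, not validity. The between-arm tests in section 2.12 are valid but give up precision that the collected visit-1 values could supply. The size of that loss rests on an assumed correlation and, for the percentages, on equal variances; its direction rests on neither, beyond the one degree of freedom. The paired tests are the more consequential part. Their P-values cannot support the comparative aim in section 2.1, and with equal moderate change in both arms they give a misleading split nearly half the time at either sample size. Because the trial is a pilot, this is a change that should be made, not a fatal defect.

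**What to change.** In section 2.12:

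- Make the between-arm analysis of each continuous outcome that has a visit-1 value an ANCOVA with that value as covariate, reporting the adjusted arm difference with its 95% CI. A mixed model over visits 4 to 10 with the same covariate is an option. It is not interchangeable with a single-visit ANCOVA when visits are missed. The choice of the main visit for each outcome is a separate decision that this change does not settle.
- Keep the rank-sum test as a robustness check for skewed or zero-heavy cigarette counts.
- Report within-arm change as mean and SD without P-values, and state that efficacy conclusions rest on the between-arm estimate alone.

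The cost is a wording change, one degree of freedom and a modelling assumption. No new data are needed, and the software already named can fit these models.

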### 2.13. Date management and quality control

Data in this study will be collected in CRF by researcher in charge who are not related to intervention. For data confidence, documents related to study (consent from, CRF, other records) will be stored in locked space or a computer with password for 3 years after the study completion. To conduct clinical research smoothly and guarantee the quality of the research, all researchers will receive the pre-education and participate the initiation meeting before the research initiation.

### 2.14. Data monitoring

There is no need for data monitoring committee because NRT and AA are commonly used and minimally invasive interventions, but data quality will be maintained by the IRB’s regular monitoring. IRB will check whether there is an audit or study-related modification and determine the continuation of the study in a critical situation. This process will ensure the scientific validity of this study and the protection of the rights of participants.

